# The effects of bicarbonated versus acetated Ringer's solutions on acid-base status and kidney injury following orthotopic liver transplantation: Protocol for a single-centre, randomised controlled trial (The BETTER trial)

**DOI:** 10.3389/fsurg.2022.1019570

**Published:** 2022-10-20

**Keywords:** bicarbonated Ringer's solution, liver transplantation, acid-base status, acute kidney injury, acetated Ringer's solution

## Abstract

**Background:**

The ideal crystalloid fluid of choice for fluid therapy during liver transplantation is unknown. Conventional balanced crystalloids are buffered with organic anions, which requires liver metabolism to prevent matabolic acidosis and protect renal function. Therefore they can not function properly during liver transplantation. On the contrary, the bicarbonated Ringer's solution (BRS) can maintain acid-base status regardless of liver function. In this study, we aimed to test the hypothesis that, in patients undergoing orthotopic liver transplantation, compared with acetated Ringer's solutions (ARS), perioperative fluid therapy with BRS could better maintain the acid-base status.

**Methods:**

This is a prospective, single-centre, randomised controlled trial. 72 eligible patients will be randomised to receive either BRS or ARS perioperatively. The primary endpoint is the difference in standard base excess (SBE) before and after operation. Secondary endpoints include the incidence of acute kidney injury (AKI) within 48 h post operation and free and alive days to day 14 for intensive care admission, invasive ventilation, vasopressors, and renal replacement therapy (RRT).

**Discussion:**

Metabolic acidosis is common perioperatively, potentially leading to decreased renal blood flow and reduced glomerular filtration rate. The use of balanced solutions can prevent hyperchloremic metabolic acidosis, thereby avoiding AKI in some patients. However, during liver transplantation, when well-functioning liver metabolism is lacking, the organic anions in conventional balanced solutions may remain strong anions and thus fail to maintain the acid-base status, but no solid clinical evidence exists now. This study will, for the first time, provide evidence on the relative effects of BRS vs. ARS on acid-base status and renal injury in patients undergoing liver transplantation.

**Clinical Trial Registration:**

The trial has been registered at the Chinese Clinical Trials Registry (ChiCTR2100046889) on 29 May 2021.

## Background

1.

Acute kidney injury (AKI) is a common complication following liver transplantation, occurring in 29%–60% of pateints (1–4). Once it develops, regardless of the severity of AKI, it is significantly associated with increased mortality (5). A long-term cohort study conducted by the National Institute of Diabetes, Digestive and Kidney Diseases showed that, compared with patients with normal renal function, those with AKI had a hazard ratio of 1-year mortality up to 3.59 (6). The development of AKI is due to multiple factors (7–14), one of which is intraoperative and postoperative infusion of supraphysiologic chlorinated liquids (15).

During liver transplantation, fluid therapy, including crystalloids and colloids, is considered the cornerstone of perioperative management to maintain normal blood volume and preserve renal perfusion (15). The RELIEF study shows that patients undergoing liver transplantation and other major abdominal surgeries had an average fluid infusion of 3,500 ml intraoperatively and 6,146 ml within 24 h after the operation, respectively, and most of the intravenous fluids are crystalloid (16, 17).

However, the ideal crystalloid during liver transplantation remains uncertain (18). By now, normal saline (NS, 0.9% sodium chloride) is most frequently used (19, 20). Nevertheless, the chloride concentration of NS (154 mmol/L) is significantly higher than that of plasma (94–111 mmol/L), which may lower plasma strong ion difference (SID), leading to metabolic acidosis and impaired renal perfusion (21, 22). A possible alternative is balanced solution (chloride limited crystalloid) (23), which, as shown in the SMART trial, could reduce adverse kidney events in critically ill patients when compared with NS (24).

In practice, the most commonly used balanced crystalloids are buffered with organic anions, such as lactate, acetate, or malate, all of which require liver metabolism to increase SID (25). During liver transplantation, liver metabolism is suspended during the anhepatic phase and severely compromised during the early neohepatic phase (26), thus organic anions buffered solution can not function properly, thereby inducing metabolic acidosis.

On the contrary, bicarbonated Ringer's solution (BRS), introduced 11 years ago, directly replaces chloride with bicarbonate. It can increase SID regardless of liver metabolism. Previous pharmacokinetic studies showed that BRS could correct metabolic acidosis faster than lactated or acetated Ringer's solution (ARS) in shock models (26). Taken together, compared with conventional organic anion buffered balanced solutions, BRS may better maintain acid-base status during liver transplantation, but no evidence exists in the literature.

In this study, we aim to compare the effect of BRS and ARS on acid-base status and renal function in patients undergoing liver transplantation. The results of this study could also provide data to power a confirmatory Phase III study in the future.

## Methods

2.

### Aim and objectives

2.1.

The primary objective of this trial is to determine whether, compared to ARS, BRS can better maintain acid-based status as reflected by the change in standard base excess (SBE) levels in patients undergoing orthotopic liver transplantation.

Secondary objectives are to assess the impact of BRS on renal function and other clinical outcomes like the number of days alive and free of intensive care admission, invasive ventilation, vasopressors, and renal replacement therapy (RRT) to day 14 after operation. Laboratory results like bicarbonate, creatinine and neutrophil gelatinase-associated lipocalin (NGAL) levels will also be compared.

### Study design

2.2.

The present study is an investigator-initiated, single-centre, superiority, randomised controlled trial. This trial was registered at the Chinese Clinical Trials Registry (ChiCTR2100046889).

### Trial committees

2.3.

A Trial Management Committee (TMC) was formed, comprising the principal investigator and all the other co-investigators (clinical and non-clinical). The TMC is responsible for the day-to-day running of the trial. A writing and publication committee was organised for drafting the manuscript and submission of the manuscript to proper academic journals. It will also decide on the authorship of this study. An independent data safety and monitoring board (DSMB) consisting of a surgeon, an anesthesiologist, and a statistician will be organised to oversee all subjects' safety. The DSMB will review the safety report regularly and have the right to stop the trial early because of concerns about participant safety. DSMB members will not be involved in the study conduct, and all the processes will be independent of the investigators.

### Study population

2.4.

All adult patients undergoing orthotopic liver transplantation surgery admitted to the Jinling Hospital, Nanjing University, will be assessed for eligibility after admission. The inclusion and exclusion criteria are as follows:

#### Inclusion criteria

2.4.1.

1.Recipients undergoing orthotopic liver transplantation surgery;2.Age ≥18 years.3.Written informed consent.

#### Exclusion criteria

2.4.2.

1.Combined transplantation;2.Patients receiving RRT within 1 week before operation;3.Patients with increased serum creatinine (SCr) levels within 1 week before operation (Defined as SCr increased by more than 1.5 times or 26.5 μmol/L (0.3 mg/dL) from baseline. Baseline was defined as SCr levels obtained within 6 months, if not available, the upper limit of normal was set for baseline at 90 μmol/L for females/110 μmol/L for males);

A patient will be considered eligible if he/she meets the inclusion criteria and does not meet any of the exclusion criteria.

### Randomisation

2.5.

The randomisation sequence will be generated by an independent statistician using SAS Version 9.4 with a fixed block size (block size = 4). Randomisation will be stratified by the surgical methods adopted (classical orthotopic liver transplantation vs. piggyback orthotopic liver transplantation). Allocation will be in a 1:1 ratio.

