### Blinding method

2.6.

Due to the specific double-packaging of bicarbonated Ringer's solution for stabilising the concentration of bicarbonate radical, blinding to investigators will not be applicable. However, research personnel, ICU staff and other caregivers will not have access to the randomisation schedule. Allocation concealment will be maintained by using a secure, password-protected study website to randomise consenting patients.

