As the infusion of sodium bicarbonate to correct metabolic acidosis could significantly increase the pH and SBE, we worked out a standardised protocol for the use of sodium bicarbonate. The amount of sodium bicarbonate used perioperatively would also be recorded. Moreover, it is known that, compared with the piggyback technique, the classical surgical procedure involves excision of the recipient inferior vena cava (IVC), which requires cross-clamping of the IVC above and below the liver, as well as the portal vein. This results in a marked reduction in venous return and consequent haemodynamic instability (36). Therefore, patients undergoing classical liver transplantations would inevitably suffer more severe metabolic acidosis. However, both surgical approaches are widely used in the study site at the discretion of the surgical teams. Therefore, we adopted stratified randomisation to compensate for the confounding effect caused by surgical methods.

This trial has several strengths and limitations. This is the first randomised controlled trial providing high-level evidence evaluating the effect of bicarbonated Ringer's solution in patients undergoing liver transplantation. And the data will be reviewed by an independent data safety monitoring board to ensure the participants' safety. However, As a phase II RCT, the study has a relatively small sample size recruited from one centre and not sufficiently powered to detect a difffference in patient-centered outcomes like incidence of AKI post operation.

The present trial is sponsored by Jinling Hospital of Nanjing University, which is the municipal centre for liver transplantation performing more than 120 liver transplantations annually. Thus the study is expected to be concluded within a year.

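### A fixed, stated block size of 4 at one centre with unblinded investigators lets an observer deduce about one allocation in three, which weakens concealment without removing it

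*Protocol article*

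**What the plan says.** Section 2.5 (Randomisation) of the protocol article has an independent statistician generate the sequence "using SAS Version 9.4 with a fixed block size (block size = 4". It adds "Randomisation will be stratified by the surgical methods adopted", with classical and piggyback transplantation as the two levels, and "Allocation will be in a 1:1 ratio".

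Section 2.2 (Study design) describes the trial as "investigator-initiated, single-centre, superiority, randomised controlled trial". Section 2.6 (Blinding method) concedes that, because of the double packaging of the bicarbonated solution, "blinding to investigators will not be applicable".

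Section 2.6 then offers two safeguards: "research personnel, ICU staff and other caregivers will not have access to the randomisation schedule", and "Allocation concealment will be maintained by using a secure, password-protected study website to randomise consenting patients". Varied or undisclosed block sizes are not among them; section 2.5 states the opposite.

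On the stratifying factor, the Discussion (section 3) says that "both surgical approaches are widely used in the study site at the discretion of the surgical teams".

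**The concern.** Both safeguards in section 2.6 protect the list. Neither stops a person from working out the next entry from entries already seen. With blocks of 4, the fourth allocation in a block is fixed by the first three, and the third is fixed whenever the first two match. Using this takes three pieces of knowledge: the block size, the stratum, and the earlier allocations in that stratum. The block size is printed in the trial's own article, so it is not confined to the statistician. The stratum is the operation itself. The earlier allocations are open to investigators at a single site.

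At stake is selection at entry. A person who expects a particular arm could approach a patient, or time the consent discussion, differently. That can shift prognosis between the arms, and adjustment for measured baseline factors would correct it only in part.

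**Working it through.** **The plan's own figures.** The article gives no figure for predictability. The only figure that can be recomputed is the sample size in section 2.11: a difference of 1.7 mmol/L, SD 2.5 mmol/L, two-sided alpha 0.05, power 80%, loss 5%.

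n per arm = 2 × (1.960 + 0.842)² × 2.5² / 1.7² = 33.95, so 34. Then 34 / 0.95 = 35.8, so 36 per arm and 72 in total, as stated. The point below does not affect it.

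**Certain allocations, fixed blocks of 4.** A 1:1 block of 4 has 6 possible orders, hence 6 × 4 = 24 allocations. An allocation is certain when one arm has no places left in the block.

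- Positions 1 and 2: never certain.
- Position 3: certain in 2 of 6 orders (the first two match).
- Position 4: certain in 6 of 6 orders.
- Total: 8/24 = 33.3%, or 1.33 per block.

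With 72 patients in complete blocks: 18 × 1.33 = 24. If both strata end two patients into a block, there are 17 complete blocks and the last four patients add none: 17 × 1.33 = 22.7, or 31.5%. Over all splits of 72 between the strata the range is 22.7 to 24 patients.

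**Best guess, fixed blocks of 4.** The observer guesses the arm with more places left and tosses a coin when the places are equal.

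- Equal places: 10 of 24 (position 1 in 6 orders, position 3 in 4), giving 5 correct on average.
- Unequal places: 14 of 24, with 12 correct and 2 wrong.
- Success: (12 + 5)/24 = 17/24 = 70.8%, against 50% under simple randomisation.

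**Varied block sizes.** These come from 4,000 simulated trials of 72 patients, each size equally likely. The observer knows the set of sizes and all past allocations but not the sizes drawn, which is generous to the observer if the set is also withheld. Strata are split 36/36; a 54/18 split gave almost the same results for the varied schemes.

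| Scheme | Certain | Best guess correct |
|---|---|---|
| Fixed 4 | 33.3% | 70.8% |
| 4, 6 | 5.6% | 68.9% |
| 2, 4, 6 | 3.9% | 69.9% |
| 4, 6, 8 | 2.3% | 67.5% |

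Under 4, 6 and 8, 0.023 × 72 is fewer than 2 patients, against about 24.

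**What selection could do: a scenario only.** Suppose that patients entered on a guess of the bicarbonated arm differ by d in expected change of SBE from those entered on a guess of the acetated arm. If selection acts at every position with unequal places, the arm means differ by d × (2 × success − 1). The article gives no value for d; 0.5 and 1 mmol/L are assumed.

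- Fixed 4: factor 2 × 0.708 − 1 = 0.417, giving 0.21 and 0.42 mmol/L (12% and 25% of the 1.7 target).
- 4, 6, 8: factor 2 × 0.675 − 1 = 0.35, giving 0.18 and 0.35 mmol/L (10% and 21%).

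On this scenario the change in blocks removes only about 0.03 to 0.07 mmol/L.

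**The case against.** Several points on the other side stand.

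- **Selection has limited room.** Section 2.4 has all adult recipients at the hospital assessed, and the criteria are objective: age, operation, consent, combined transplantation, recent renal replacement therapy and a numeric creatinine rule. The Discussion gives more than 120 transplants a year, so 72 patients is up to about 72/120 = 60% of a year's caseload before exclusions and refusals. This narrows the opening. It does not close it, because whom to approach and when remains a human decision.
- **The list is independent and withheld.** The next assignment is not disclosed in advance, and the one-third figure applies only to someone who knows the block size and keeps a tally by stratum. That is feasible at one unblinded site, but it is an assumption about behaviour. The article does not say who enrols.
- **The proposed change leaves most of the guessability.** This is correct, and the change should be offered on those terms.
- **The outcome is a laboratory value.** That limits biased assessment. It does not prevent selection at entry.

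Three stronger readings are tempting. A reader might infer that the result will be biased by about 0.42 mmol/L; that figure rests on an assumed 1 mmol/L difference which the article does not support, and most of it would remain under varied blocks. A reader might infer that a surgical team could steer a patient into the stratum with the preferred next allocation, given that technique is discretionary. The article does not say whether technique is fixed before the allocation is released, a sequence commonly left to the full protocol, so this is a possibility and no more. A reader might also infer that no analysis could repair such bias; adjustment can reduce the part due to measured prognosis, though not selection on unmeasured factors.

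The block size is stated outright, so this is a criticism of a stated choice and not of a detail left to another document.

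**Conclusion.** The point holds as a weakness of design. Fixed blocks of 4, together with a single centre, unblinded investigators and strata known to staff, make about one third of allocations deducible with certainty (31.5% to 33.3%, about 23 to 24 of 72) and 70.8% guessable in complete blocks. The website and the withheld schedule do not address this, so section 2.6 claims more for concealment than the scheme delivers.

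The percentages follow exactly from the block design, for an observer who knows the block size and sees earlier allocations by stratum. Whether anyone used that knowledge is unknown, and nothing in the article suggests it. The range of 0.21 to 0.42 mmol/L is an illustration under assumed inputs and should not be read as an estimate of bias. The improvement is worth making because it is cheap; the trial is not shown to be compromised.

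**What to change.** **If allocations remain to be made:** generate them with randomly varying permuted block sizes within strata, for example 4, 6 and 8. The independent statistician should hold the sizes and the list, with no disclosure until enrolment ends. Section 2.5 should then say only that block sizes vary and are withheld.

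The programming is minor, but changing the scheme during the trial needs a protocol amendment. Balance loosens slightly: an unfinished block can leave a stratum out of balance by at most half the block size, so the worst case over two strata rises from 2 + 2 = 4 patients to 4 + 4 = 8. The sample size does not change.

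**If enrolment is complete:** registration was in May 2021, publication in October 2022 and the expected duration was within a year, but the article does not give enrolment status. In that case the report should state the fixed block size and the resulting predictability as a limitation, and should not present the website as sufficient concealment. A table of baseline characteristics by predicted allocation would help readers judge whether selection is likely. This costs a few sentences and one table.

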### Blinding method

2.6.

Due to the specific double-packaging of bicarbonated Ringer's solution for stabilising the concentration of bicarbonate radical, blinding to investigators will not be applicable. However, research personnel, ICU staff and other caregivers will not have access to the randomisation schedule. Allocation concealment will be maintained by using a secure, password-protected study website to randomise consenting patients.

### Study interventions

2.7.

The only difference between the two study groups exists in the choice of perioperative intravenous isotonic crystalloid: bicarbonated Ringer's solution (BRS group) vs. acetated Ringer's solution (ARS group). The compositions of each crystalloid solution are displayed in Supplementary Table S1.
•*Group 1: BRS group*
Patients will receive bicarbonate Ringer's solution for fluid therapy during and within 48 h post operation.•*Group 2: ARS group*
Patients will receive acetate Ringer's solution for fluid therapy during and within 48 h post operation.

### Management of liver transplantation

2.8.

First, both groups received general standard of care involving the following key components (27). The operating room temperature will be set at 22°C and standard warming measures be used for all patients. All patients will receive standard general anaesthesia induced by midazolam, sufentanil, etomidate, cisatrcurium and maintained by propofol, remifentanil, sevoflurane and additional injection of sufentanil. An arterial line and a central venous catheter will be inserted before induction of anaesthesia. Mechanical ventilation will be performed routinely. During the perioperative period, all patients will receive intravenous fluids according to a standardised protocol, which includes basiliximab, antibiotics, esomeprazole and methylprednisolone. Transfusions will be administered at the discretion of the attending anaesthetist according to the National Blood Transfusion guidelines.

Throughout the operation, arterial blood gas will be measured every 60 min during the dissection phase, every 30 min during the anhepatic phase (including a 5-min pre-reperfusion blood gas) and every 30 min during the neohepatic phase for 1 h (including a 5-min post-reperfusion blood gas), then hourly until surgical closure. When pH is less than 7.2 or SBE is less than −10 mmol/L, additional 5% sodium bicarbonate will be infused with a total amount of 5% NaHCO_3_(ml) = (−2.3-SBE)*weight (kg)*0.42 to correct acidosis. The infusion will be started at a rate of 90 ml/h and discontinued with a targeted pH level of 7.35.

When the operation is completed, all the patients will be transferred to the surgical Intensive Care Units for postsurgical care. Both groups will receive standard treatment according to the guidelines after admission (27), including continuous vital signs recording, adequate fluid therapy, routine medical treatment (blood glucose control, antibiotics if needed and sedatives if required), organ support measures, etc. Organ failure would be assessed on a daily basis according to the SOFA score.

Initiation of RRT should be based on the criteria described by Bellomo et al. (28). Patients who have AKI (at least 1.5 times increase in creatinine from known baseline value) and meet predefined specific criteria will be eligible for initiation of RRT.

### Endpoints

2.9.

#### Primary outcome measure

2.9.1.

The primary outcome measure is the change of SBE during the operation, reflected by the difference in SBE measure before and after the operation (ΔSBE = SBE_post_-SBE_pre_). SBE_pre_ will be measured before introduction of anaesthesia, and SBEpost will be measured shortly before transportation to the surgical ICU.

#### Secondary outcome measures

2.9.2.

##### Part I: Process measures

2.9.2.1.

1.The amount of BRS/ARS used during operation and within the first 2 days post operation;2.Additional sodium bicarbonate used during operation and within the first 2 days post operation;3.Serum acetic acid concentration before operation, 5 min post reperfusion of the donor liver, 0, 6, 12, 24 and 48 h post operation.

